## Discussion

Advancements in HNC diagnostics and treatments have led to an improvement in survival over the past decade [35]. These improvements are highly creditable but need to be followed by effective aftercare of cancer survivors, since functional and financial vulnerability are strongly associated with survivorship. From previous research, it is evident that many HNC survivors experience long-term oral sequelae, such as hyposalivation, pain, and radiation-induced dental caries [4]. These complications significantly impact HRQoL, even after successful cancer treatment [18, 19]. Although substantial evidence underscores the critical role of dental care for HNC survivors, its systematic integration into oncologic treatment regimens remains a complex and persistent challenge.

To date, few interventions targeting oral health in HNC have been evaluated using RCT methodology [36–38]. All the identified studies included fewer than 100 participants, and none followed patients for more than one year. Reported interventions comprised either professional oral care (e.g., tooth brushing instructions, professional mechanical tooth cleaning, and fluoride varnish application) [37], an integrated supportive programme (including oral hygiene instructions, oral health self-care strategies, facial and tongue muscle exercises, and salivary gland massage) [36], or an oral health programme (with oral health education, fluoride varnish application, and fluoride mouth rinsing) [38]. To the best of our knowledge, this will be the first RCT among HNC survivors to evaluate a comprehensive oral health program and its impact on both physical and psychological well-being over an extended follow-up period. If the intervention demonstrates promising outcomes, it will provide novel insights into effective strategies to mitigate oral complications and improve long-term oral health and quality of life in this population.

There are important methodological considerations that need to be acknowledged. Given the study design and intervention, blinding will not be feasible. This will pose a particular challenge regarding the PROMs [39]. When an intervention is delivered through direct human interaction, there is an inherent risk that attention bias will affect PROMs. Hence, improvements in PROM scores may not solely reflect the intervention itself but could also result from increased frequency of patient–provider contact. Additionally, patients who are aware of receiving an intervention may report improvements more positively. When using PROMs, there is a risk that patients may adapt to their condition or treatment sequelae, leading to changes in PROM scores that reflect adaption rather than true changes in symptoms. We believe that using PROM instruments will add substantial value and enable us to demonstrate the therapeutic benefit of the oral health care programme from the patient’s perspective. To address the previously described potential biases associated with using PROMs, and to add objectivity, the outcomes measured are not based solely on PROMs but instead on a combination of patient-reported outcomes, clinical indicators, imaging, and biochemical biomarkers.

The extensive data collection is a strength and will enable us to investigate the longitudinal impact of the oral health care programme. To enhance the generalizability of the findings, a diverse and inclusive cohort of patients with HNC, representing different tumour sites, stages, and treatment modalities, will be recruited. We will use REDCap [25] for randomisation, which enables instant and consistent allocation according to a predefined scheme, thereby reducing the risk of human error. The planned feasibility study is an additional strength, as it will enable us to resolve methodological issues early and identify where modifications are necessary to strengthen trial methodology and operational processes [33].

The planned economic evaluation is important, as financial incentives drive decisions to implement new methods within existing healthcare services [40]. The growing financial burden of cancer care highlights the importance of aligning healthcare resource allocation with clinical benefit across various domains of care [41, 42]. We acknowledge that both registered sickness absence and included cost estimates have inherent limitations, as they may not fully capture changes in disease burden and are often based on approximate or standardised valuations. Consequently, economic evaluation does not directly translate into a clinical decision but does constitute one of several tools to inform it.

A male/female perspective is also highly relevant in this project, as HNC shows substantial sex differences in incidence with a male predominance [1]. This sex difference necessitates the inclusion of both biological and lifestyle factors in the analysis. For example, smoking, alcohol consumption, human papillomavirus (HPV) infections, and healthcare-seeking behaviours may vary between sexes and contribute to variations in disease onset and treatment-related side effects (including oral complications). Identifying potential sex-related differences in functional impairment and the effectiveness of the planned intervention is crucial when evaluating new methods for use in health care.

This study has important clinical implications, and its results will be freely available through open-access journals and plain language summaries for both the public and healthcare professionals. It addresses a growing patient population whose rehabilitation needs are well documented, yet often inadequately met. It also highlights oral health as a critical factor influencing physical, psychological, social, and economic outcomes in HNC survivors. The findings have the potential to inform recommendations for integrating oral care into routine follow-up, thereby promoting equity and structured monitoring of oral health after HNC treatment.

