### Intervention and standard of care

The oral health care programme is a practice-led intervention that was developed by a multidisciplinary team of healthcare professionals and researchers (physicians, nurses, dentists, dental hygienists, and a dietitian), and in close collaboration with HNC survivors. The intervention starts 6 months after completion of RT and ends after the 3-year follow-up. Every 3 months, participants in the intervention group are scheduled for an appointment with a dental hygienist. During these visits, participants are asked about oral hygiene habits, fluoride use, dietary habits (with focus on intake of easily degradable carbohydrates), and oral dryness. The dental hygienist also performs a thorough examination of the oral cavity, assessing signs of dental problems (e.g., tooth decay) or gum problems (e.g., gingivitis or periodontitis).

The intervention is individually tailored and based on the examination and the patient’s report. It includes oral and written advice, and recommendations from the dental hygienist, e.g., how to increase oral hygiene using the correct toothbrushing technique, interdental cleaning, or strategies to address oral dryness. It also includes tailored preventive professional oral hygiene treatment, e.g., plaque and dental calculus removal, fluoride gel application, and polishing to produce a smooth and clean surface. All visits to the dental hygienist are at no cost. If oral problems are beyond the competence of the dental hygienist, dentists are consulted and the participant pays for any necessary treatment.

At the 6-month follow-up, patients are randomised to receive the intervention (oral health care programme) or standard of care, which in Sweden only includes dental care for up to approximately 3 months following treatment. Within standard of care, patients therefore need to actively seek dental care and support themselves after 6 months. Patients who have undergone RT targeting the oral cavity may be entitled to a partial allowance, which subsidies preventive dental care; however, not all patients receive this benefit, and it does not cover all the costs.

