#### Data collection overview

Clinical/research nurses, dentists and dental hygienists at each site are responsible for the data collection. Data are collected from all participants at baseline, 6 months after the end of treatment (randomisation and start of intervention), and 1, 2 and 3 years after randomisation. Non-adherence and non-retention are registered.

Data gathered through history taking or medical records include, e.g., demographics (sex, age and education), as well as information on diagnosis and treatment (tumour site and stage, treatment modality, comorbidities and medication), work ability and sick leave, eating ability, and habits, including use of nicotine and alcohol, nutritional status (anthropometrics, body composition). Body composition measurements using calf circumference are performed on all participants. Bioelectrical impedance analysis (Bodystat^®^ Multiscan 5000) is used on a subgroup.

In addition, participants complete questionnaires (PROMs) to assess HRQoL, depression, anxiety and stress, health status, self-efficacy, and self-rated oral health (Table 1). The questionnaires are completed digitally or on paper.

**Table 1 Tab1:** Data overview from patient-reported outcome measures, PROMs

Questionnaire	Description
European Organization for Research and Treatment of Cancer Quality of Life Questionnaire-Core 30 (EORTC-C30) [26]	Assesses health-related quality of life in cancer patients. Comprises 30 items covering, e.g., global health status, functional domains (physical, role, emotional, cognitive, and social), symptom scales (fatigue, pain, nausea/vomiting).
EORTC-Head and Neck Cancer Module (EORTC-HN43) [27]	Assesses health-related quality of life in patients with head and neck cancer, an updated version of HN35. Includes 43 items addressing disease- and treatment-specific issues, such as swallowing, speech, senses (taste and smell), pain, social eating, sexuality, and body image, as well as symptoms such as dry mouth and sticky saliva.
Depression Anxiety Stress Scale-21 (DASS-21) [28]	Measures negative emotional states. Consists of 21 items divided into three subscales assessing symptoms of depression, anxiety, and stress.
EQ-5D-3 L [29, 30]	Measures general health status. Consists of five dimensions (mobility, self-care, usual activities, pain/discomfort, and anxiety/depression). Each dimension has three levels of severity.

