General Self-Efficacy (GSE) [31]	Assesses an individual’s perceived ability to cope with a variety of demanding situations. Consists of 10 items measuring self-belief related to problem-solving and adaptation.
Self-Perceived Oral Health (SPOH) [32]	A modified version of the SPOH instrument is used to assess subjective oral health. The instrument includes items on self-rated oral health (12 items), oral health behaviours (8 items), perceived oral health knowledge (4 items), and future perspectives (2 items).

Data on oral health (number of remaining teeth, maximum interincisal opening [MIO], caries and periodontal status) are collected during clinical examination. Participants are asked how often they have sought dental care. Computed Tomography (CT) and Cone-Beam Computed Tomography (CBCT) are used to detect pathological changes in the jaw (osteoradionecrosis). Blood and saliva samples are collected for analysis and long-term storage (biobanking). Blood samples are analysed for haematology and immune parameters, including markers of inflammation. The stimulated whole salivary secretion rate is determined, and the buffering capacity is assessed. For a subgroup of participants, saliva composition (proteins, ions, metabolites and inflammatory biomarkers) and the oral microbiome will be analysed.

Register data will be obtained from the National Board of Health and Welfare (National Prescribed Drug Register, National Register of Care and Social Services for the Elderly and Persons with Impairments, National Register of Interventions in Municipal Health Care, National Cause of Death Register, National Patient Register, National Dental Health Register) and from the Swedish Social Insurance Agency (Micro Data for Analysis of Social Insurance [MiDAS] database, Dental care). Register data on healthcare utilisation will also be obtained for a subgroup of patients. Register linkage will be performed using personal identity numbers, and the data will be pseudonymised after data collection.

The collected register data will cover the period from one year prior to diagnosis to five years after the completion of treatment, and will include information about, for example, prescribed drugs, municipal health and social care, specialised outpatient and inpatient care, registered sickness absence, and costs related to functional impairments, as well as dental healthcare.

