### Feasibility testing

The feasibility of the intervention will be tested after the 6-month follow-up, once participants have been randomised. The first randomised participants will be asked to take part in the feasibility testing. We will use individual and/or focus group interviews with a sample of participants (*n* = 10) and also with a subgroup of healthcare providers responsible for recruiting participants to the study and conducting the data collection and intervention (dental hygienists, clinical/research nurses, *n* = 10). Interviews will follow a semi-structured format based on a predefined guide. The aim is to explore the feasibility and acceptability of the data collection procedures for primary and secondary outcome measures, as well as the intervention itself [33]. Additionally, we will review recruitment and retention rates, completeness of outcome measure data, and practical aspects of data collection. Protocol modifications will be implemented if suggested by the feasibility testing results. Data from the HNC survivors participating in the feasibility testing will be included in the final analysis, provided that any adjustments to the oral health care programme do not compromise the study’s integrity.

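### Blinding is ruled out for everyone on grounds that cover only participants and treating staff, so the examiner-judged outcomes offered as objective support for the PROMs may be scored with knowledge of the arm

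*Protocol article*

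**What the plan says.** On blinding, the Discussion is unqualified: "Given the study design and intervention, blinding will not be feasible". It names one consequence, "This will pose a particular challenge regarding the PROMs", and explains it by personal contact between patient and provider, by patients knowing that they receive an intervention, and by adaptation to symptoms over time. Its answer to these biases is that "the outcomes measured are not based solely on PROMs but instead on a combination of patient-reported outcomes, clinical indicators, imaging, and biochemical biomarkers".

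On who does what:

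- Intervention and standard of care: "Every 3 months, participants in the intervention group are scheduled for an appointment with a dental hygienist". The hygienist also examines the mouth for decay and gum disease at these visits. Dentists are consulted when a problem exceeds the hygienist's competence.
- Data collection overview: "Clinical/research nurses, dentists and dental hygienists at each site are responsible for the data collection".
- Feasibility testing describes a group of providers as "conducting the data collection and intervention (dental hygienists, clinical/research nurses", with recruitment among their shared tasks.
- Data collection overview, on the clinical outcomes: "Data on oral health (number of remaining teeth, maximum interincisal opening [MIO], caries and periodontal status) are collected during clinical examination". No examiner is named. CT and CBCT serve to detect osteoradionecrosis, and no reader is named.

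**The concern.** The article takes a position on blinding and builds an argument on it. It concedes that knowledge of allocation can bias the PROMs and offers clinical and imaging outcomes as the counterweight. That counterweight works only to the extent that those outcomes are less exposed to knowledge of allocation. If blinding is ruled out for everyone, an examiner who knows the arm may score them, and one profession both delivers the programme and collects data.

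At stake is the interpretation of the oral-health half of the trial's hypothesis, which is that the programme improves both oral health and HRQoL. If PROMs and judged clinical outcomes both favour the programme, the agreement is persuasive only if the two do not share a source of bias.

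**Working it through.** The plan gives no figure on this point, so there is none to reproduce. The check sets the statements side by side.

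**Step 1: does the stated reason support the stated scope?** The reasons in the Discussion concern people who give or receive face-to-face care. A radiology reader given an image with a study code has no such contact. A dental examiner who does not treat the participant and is not told the arm can be at least partly masked. The conclusion is therefore wider than its justification.

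**Step 2: is there an overlap of roles?** By profession, yes. Intervention and standard of care assigns delivery to hygienists, Data collection overview includes hygienists among the data collectors, and Feasibility testing names hygienists and nurses together for both tasks. By individual, the text is open: nothing says that the treating hygienist scores the same participant, and nothing prevents it.

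**Step 3: does another safeguard cover this?** Allocation and follow-up keeps the randomisation list from the research team. That protects allocation up to randomisation. It does not mask assessments made 1, 2 and 3 years later.

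**Step 4: which outcomes are exposed?**

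| Outcome | Room for examiner judgement |
|---|---|
| Caries, periodontal status | Substantial: scored at examination |
| CT/CBCT reading for osteoradionecrosis | Substantial, but easily masked |
| Mouth opening (MIO) | Some: a measurement, but taken by an examiner |
| Remaining teeth | Little: a count |
| Saliva and blood measures | Little |
| Register data | None at the examination |
| PROMs, including the primary outcome | Patient-reported; masking examiners does not help |

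**Step 5: what would a scoring difference do?** Let the true difference between arms be Δ, and let knowledge of the arm shift scores on average by b₁ in the programme arm and b₀ under standard of care. The expected estimate is Δ + (b₁ − b₀). The standard error falls as participants are added; the term b₁ − b₀ does not. The planned 300 participants therefore give no protection against it. The documents contain nothing from which to estimate b₁ − b₀, and this derivation does not show that it differs from zero.

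**Step 6: is there time to act?** Inclusion began in September 2025, before treatment. Randomisation follows 6 months after treatment ends, and the first post-randomisation examination 1 year later. September 2025 plus 6 months plus 12 months is March 2027, before adding the length of treatment. The article is dated September 2026, so on its own timetable no 1-year examination had yet taken place.

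**The case against.** The strongest reply has four parts.

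First, the overlap is inferred. Nurses, dentists and hygienists share responsibility for a long list of tasks, including history, questionnaires, body measurements, samples and examinations. Dentists may already do the scoring. This stands in part: a reader might infer that hygienists score the results of their own care, but the article does not say so. It only leaves the possibility open.

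Second, a journal article condenses a fuller protocol, and masked reading, coded samples and masked arm labels are details commonly left to that document or to the analysis plan. This would answer a complaint about silence, and silence about laboratory coding or analysts is not a fault here. It does not answer a blanket statement that blinding is infeasible, which, followed as written, gives no reason to mask anyone.

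Third, the sentence sits in a discussion of PROMs and may have been meant for participants and providers only. That is a plausible reading, and if it is right, limiting the wording costs nothing.

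Fourth, a reader might infer that most of the quantitative oral-health outcomes are unprotected. The documents do not support that. Tooth counts, laboratory measures and register data are little exposed, and the article claims only added objectivity, not independent confirmation.

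It is also fair to say that a site dentist is not masked merely by being a dentist, and may be consulted about a programme participant. The fix has to allow for this.

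**Conclusion.** The point holds in a limited form. The statement on blinding is broader than its reasons, and it undercuts the use made of clinical indicators and imaging in the same paragraph. The exposure is confined to examiner-judged secondary outcomes: caries, periodontal status, CT/CBCT reading for osteoradionecrosis and, to a lesser degree, mouth opening. No numerical size can be given. Any differential scoring would pass unreduced into those estimates.

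The conclusion rests on two assumptions: that scoring of these outcomes involves judgement that knowledge of the arm can influence, and that no unseen document already provides for masked or separate assessment. It does not rest on the same hygienist treating and assessing a participant, which would make matters worse but is not stated. It has no bearing on bias in the patient-reported primary outcome, which remains either way.

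**What to change.** 1. Limit the infeasibility statement to participants and treating staff.
2. Have CT/CBCT read for the trial under study code, without arm information. Data security already provides for coding lists with limited access.
3. Run the main analysis on masked arm labels.
4. Have the 1-, 2- and 3-year caries and periodontal examinations scored by existing site dental staff who do not treat that participant and are not told the arm. A dentist consulted about a programme participant should not score that participant.
5. Where a site cannot do this, record it, and do not present those outcomes from that site as an objective check on the PROMs.

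The cost is protocol wording, coded image handling and examination scheduling. Some rostering burden will fall on small sites; the article gives no staffing figures, so its size is unknown. Patients will occasionally reveal their arm to the examiner. Feasibility testing already foresees changes to the protocol after review of the data collection procedures, so the change has a natural place.

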## Data Availability

No datasets were generated or analysed during the current study.

## Abbreviations

CRT: Chemoradiotherapy
CT: Computed Tomography
CBCT: Cone-Beam Computed Tomography
DASS-21: Depression Anxiety Stress Scale-21
EORTC-C30: European Organization for Research and Treatment of Cancer Quality of Life Questionnaire-Core 30
EORTC-HN43: European Organization for Research and Treatment of Cancer Quality of Life Questionnaire - Head and Neck Cancer Module
EORTC QLQ-HN35: European Organisation for Research and Treatment of Cancer Quality of Life Questionnaire – Head and Neck Module
GSE: General Self-Efficacy
HNC: Head and neck cancer
HRQoL: Health-related Quality of Life
ITT: Intention-to-treat
MIO: Maximum Interincisal Opening
MiDAS: Micro Data for Analysis of Social Insurance
PROM/s: Patient-reported outcome measure/s
RT: Radiotherapy
RCT: Randomised controlled trial
REDCap: Research Electronic Data Capture
SACT: Systemic anti-cancer therapy
SPIRIT: Standard Protocol Items: Recommendations for Interventional Trials
SPOH: Self-Perceived Oral Health
QALYs: Quality Adjusted Life Years
